#### Conversion to surgery

The criteria for conversion to surgery are based on an overall clinical evaluation conducted in collaboration with the patient. In the non-surgical group, the primary reason for conversion is persistent severe pain after 6–12 weeks. In the surgery group, adverse events can serve as reasons for conversion to RSA. Patients who discontinue for reasons unrelated to surgery will be documented and recorded. Patients receiving osteosynthesis or RSA will also have follow-up assessments after 6, 12, and 24 months.

## Statistical methods

### Hypothesis

The null hypothesis is that the shoulder function measured with OSS 12 months after surgery is not superior to non-surgical treatment.

The alternative hypothesis is that the shoulder function measured with OSS 12 months after surgery is superior to non-surgical treatment.

### Sample size and power considerations

The standard deviation (SD) for OSS has been reported as 12 [34]. While the minimal clinically important difference (MCID) for the OSS (0–48) has been reported to range from 5 to 6.9 points in various shoulder diseases, age groups, and assessment points, it has not been established for PHF [35]. Without a patient-derived MCID for PHF, a relevant difference of 9.6 was assumed to represent a clinically meaningful difference. This corresponds to approximately a 20% difference between the surgical group and the non-surgical group on a 0–48 OSS scale. Based on this assumption, with a power of 80% and a 5% level of significance, a sample size of 25 patients per group is required. Assuming for a 15% potential loss to follow-up, the recruitment target is 30 patients in each group, resulting in a total of 60 patients. The recruitment period is expected to be 24 months.

### Statistical analysis

The statistical analysis plan is available within Supplementary Information, file 2.

Baseline characteristics will be presented using descriptive statistics. We will compare the following patient characteristics between the groups at baseline: age (categorized into 5-year age groups), sex, height, weight, ASA score, fracture classification (Neer [5]), dominant arm (yes/no), smoking, alcohol consumption, educational level, working status, work type, osteoporosis (three-level ordinal variable based on *T*-scores (osteoporosis, osteopenia, and normal bone density)), and clinical frailty scale [36]. SD will be reported, and *n* (%) for categorical values.

Osteoporosis will be collected and reported descriptively as a three-level ordinal variable based on *T*-scores (osteoporosis, osteopenia, and normal bone density).

The OSS results for surgical and non-surgical treatment groups at 6, 12, and 24 months will be tabulated and graphically represented with mean, SD, median and IQR according to the distribution.

The primary outcome, OSS at 12 months, will be analyzed using two-sample *t*-test comparing the two treatment groups. Normality assumptions will be assessed, and if violated, alternative methods such as transformation or non-parametric Mann–Whitney *U* test will be considered. As suggested in the extension of the CONSORT 2010 statement, the primary outcome will be analyzed for the intention-to-treat (ITT) population.

In addition, linear mixed models will be used to analyze OSS and EQ-5D over time (6, 12, and 24 months) accounting for the repeated measures structure and to explore outcome trajectories. Model-based contrasts from the LMM will be used to estimate adjusted between-group differences at specific time points. Missing data will be handled within the mixed model framework, assuming data are missing at random. Details are provided in Supplementary Information, file 2.

We will record and report adverse events in each group. At the 6-month follow-up, patients will be asked, and we will record and report the length of rehabilitation in municipalities (in weeks) and whether the patient has followed the rehabilitation plan.

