### Participants

Patients will be recruited from the orthopedic departments at Zealand University Hospital in Denmark and Tampere University Hospital in Finland.

The following inclusion criteria will apply:Patients aged between 50 and 65 years with a displaced proximal humerus fracture after a low-energy trauma.Patients should be cognitively capable of answering the follow-up questionnaires.

The following exclusion criteria will apply:

Communication:The patient does not understand written and spoken native language (Danish or Finnish)Inability to give informed consent

Fracture criteria:Fractures assessed to be non-reconstructable by the treating surgeonIsolated tuberosity fracture, fracture dislocations, open fractures, and fractures with involvement of the articular surfaceLess than 25% contact between the humeral head and humeral shaft measured at two perpendicular radiographs at 2 weeks postinjuryPathological fractures or previous fractures in the same proximal humerusConcomitant fractures, which could influence the outcome

Other criteria:

Paralysis of the upper extremity

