### Randomization and concealment of allocation

We will use Research Electronic Data Capture (REDCap) [23] to generate an irreversible randomization sequence. A person not involved in the project will generate and upload the allocation table using “R.” All investigators will be blinded to the allocation table. The person not involved in the project will have no access, including no access to the data. We will be using block randomization with varying block sizes of 4 and 6, stratified by location. REDCap will conceal the sequence for the investigators before allocation takes place. Enrolment and allocation will occur on-site by LH, AL, BS, or LK. A REDCap built-in functionality ensures that only patients who meet all inclusion and no exclusion criteria can be randomized.

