#### Non-randomized cohort

Patients who declined randomization but consented to follow-up will form the non-randomized cohort. Baseline characteristics will be summarized descriptively and compared between the randomized and non-randomized cohorts, as well as among the non-randomized patients by treatment choice. The primary outcome (OSS at 12 months) will be analyzed by treatment modality. Secondary outcome measures (OSS and EQ-5D) will be presented descriptively and graphically at 6, 12, and 24 months. Analyses will include multivariable linear regression adjusted for baseline covariates; propensity score methods may be applied. The incidence and timing of salvage procedures will be described and analyzed using Cox proportional hazards models.

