## Data Availability

Data sharing is not applicable to this article as no datasets were generated or analyzed during the current study. The Data Protection Agency of Region Zealand has approved the handling of personal data (p-2024–16591). Compliance with the General Data Protection Regulation (GDPR) and the Danish Data Protection Act will be ensured at all times. A data processing agreement has been signed in both recruiting centers. Research data is stored on REDCap, a secure online patient management program, accessible only to LH, SB, AL, BS, and LK on a secure server at Region Zealand University Hospital (with two-factor authentication login). The primary investigator will have access to the final data set. The REDCap setup ensures that randomization is only possible, if all baseline information is entered correctly. All data will be fully anonymized before publication. The trial results will be published in an open-access peer-reviewed journal.

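### Randomisation is stratified by location, but the primary t-test leaves site out; it stays valid, yet is conservative and less precise if the two centres differ

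*Protocol article*

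**What the plan says.** **Randomisation.** The section Randomization and concealment of allocation states: "We will be using block randomization with varying block sizes of 4 and 6, stratified by location". Under Participants the centres are "Zealand University Hospital in Denmark and Tampere University Hospital in Finland", so the stratification factor has two levels, one per country.

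**Primary analysis.** Under Statistical analysis: "The primary outcome, OSS at 12 months, will be analyzed using two-sample" *t*-test. If normality fails, a transformation or a Mann–Whitney test will be considered. No site term or covariate is named for any of these.

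**Other analyses.** The same section adds linear mixed models over 6, 12 and 24 months: "Model-based contrasts from the LMM will be used to estimate adjusted between-group differences at specific time points". These are introduced as additional to the primary test. The article does not name the adjustment variables and refers to Supplementary file 2 for details. For the non-randomised cohort the article says: "Analyses will include multivariable linear regression adjusted for baseline covariates".

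**Baseline data.** The listed characteristics include "age (categorized into 5-year age groups), sex, height, weight, ASA score, fracture classification". For the randomised trial, their stated use is a comparison of the arms at baseline. Under Data Availability: "The REDCap setup ensures that randomization is only possible, if all baseline information is entered correctly".

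**The concern.** Stratified blocking makes the arms nearly alike on site. The true sampling variance of the difference in means is then smaller than the two-sample formula assumes whenever the centres differ in mean OSS. The unadjusted t-test still counts the site variation as noise. Its standard error is then too large, its real type I error falls below 5%, and its interval is too wide.

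This matters because the design has little slack. The planned 25 evaluable patients per arm give about 79–80% power at an assumed difference of 9.6 points, and the article itself calls the sample relatively small. Some precision is lost if OSS differs between a Danish and a Finnish centre, for example through case mix, rehabilitation or the way patients answer the questionnaire. Using the factor that the design already controls would recover it.

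**Working it through.** **1. Inputs from the article (Sample size and power considerations).** Difference 9.6 points, SD 12, power 80%, significance level 5%, 25 per arm evaluable, 15% loss, 30 per arm recruited.

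**2. Reproducing the plan's figure.** The article does not state sidedness. Two-sided 5% gives

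n = 2 × (1.960 + 0.842)² × 12² / 9.6² = 2 × 7.85 × 1.5625 = 24.5, rounded up to 25 per arm.

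25 / 0.85 = 29.4, rounded up to 30 per arm and 60 in total. Both match; one-sided 5% would give 20. Exact t-test power at 25 per arm is 79.1%. The 95% CI half-width is t₄₈ × SD × √(2/25) = 2.011 × 12 × 0.283 = 6.8 points.

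**3. Adjusting for site alone.** Assumptions, none given in the article: two sites of equal size, total SD held at 12 including any site variation, and a site difference s of 0, 6 or 10 points. With equal sites, site contributes s²/4 to the variance of 144:

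- s = 6: 9/144 = 6% of variance; residual SD √(144 − 9) = 11.6
- s = 10: 25/144 = 17% of variance; residual SD √(144 − 25) = 10.9

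The site-adjusted half-width is t₄₇ × residual SD × √(2/25):

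- s = 6: 2.012 × 11.62 × 0.283 = 6.6
- s = 10: 2.012 × 10.91 × 0.283 = 6.2

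Simulation with blocks of 4 and 6 within site and 50 evaluable patients agrees:

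| Site difference | Type I error, t-test | Type I error, site-adjusted | Half-width, t-test | Half-width, site-adjusted |
|---|---|---|---|---|
| 0 | about 5% | about 5% | 6.8 | 6.8 |
| 6 points | about 4.6% | about 5% | 6.8 | 6.6 |
| 10 points | about 3.2% | about 5% | 6.8 | 6.2 |

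With no site difference, power is 79% either way. A parallel simulation with 51 evaluable patients gave power, t-test against site-adjusted, of 80% and 80% (no difference), 79.5% and 81.2% (6 points), and 81.4% and 86.8% (10 points).

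**4. Adding age, sex and Neer class.** These are not stratified, so chance imbalance inflates the variance of the adjusted estimate by about (N − 3)/(N − k − 3) for k covariate terms. At N = 50:

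- k = 3: 47/44 = 1.07; break-even where 1 − R² = 44/47, so R² = 6.4%
- k = 4 (for example, Neer class in two terms): 47/43 = 1.09; break-even R² = 4/47 = 8.5%

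Simulated power at 9.6 points, with no site effect and site plus three covariate terms in the model, against 79% unadjusted:

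| R² of the covariates (assumed) | Power | Half-width |
|---|---|---|
| 0 | 76% | 7.0 |
| 0.05 | 78% | 6.9 |
| 0.10 | 81% | 6.7 |
| 0.20 | 85% | 6.3 |

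With four covariate terms, power is 75%, 77%, 79% and 84%.

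**The case against.** **The t-test is valid.** This stands. Leaving site out causes no bias and no inflation of type I error. A reader might infer that a stratified design makes an unadjusted test wrong; at worst it is conservative, and only if the centres differ. The article gives no evidence on whether they do.

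**The plan already adjusts elsewhere.** This stands in part. The mixed model promises adjusted contrasts, and its specification in Supplementary file 2, not available for this review, may include site. But the article places that model beside the primary test, so the headline result would still be the unadjusted one.

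**Adjusting for more baseline variables would be better still.** This inference is tempting because the data are complete by design and adjusted regression is planned for the non-randomised cohort. The documents do not support it. Nothing in the article shows that age, sex or Neer class predicts 12-month OSS. Age is confined to 50–65, the exclusions narrow the fracture range, and Table 1 schedules no baseline OSS. A calculation that only shrinks the SD by √(1 − R²) and deducts degrees of freedom gives 83% power at R² 0.10 and 87% at 0.20. It omits chance imbalance and is too favourable; step 4 of the working gives 81% and 85%, with a loss at R² 0.05.

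**Age in five-year bands.** A reader might see lost information here. The article uses the bands only to describe baseline, so this is not a defect.

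**Conclusion.** The point holds for the stratification factor, as a modest matter of efficiency. The primary test ignores site although randomisation is stratified on it. Among the scenarios examined, the cost runs from nothing when the centres do not differ to a type I error of about 3.2% and 0.6 points of CI half-width at a 10-point site difference. These sizes rest on assumed site differences, equal centres, 50 evaluable patients and a total SD of 12. Because site adjustment costs nothing measurable when it is not needed, the change is worth making without knowing which scenario applies. Adjustment for age, sex and Neer class is a judgement for the trial team: it helps above an R² of roughly 6–9% and loses power below it.

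**What to change.** Define the primary analysis of 12-month OSS as a linear model with treatment and site as fixed factors, or as the 12-month treatment contrast of the planned mixed model with site included. Report the site-adjusted mean difference with its 95% CI as the primary result and keep the unadjusted t-test as a sensitivity analysis.

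If the team has outside reason to expect age in years, sex or Neer class to be prognostic, name a short list of them in advance and state the expected R². Otherwise leave them out of the primary model.

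The cost is a sentence in the protocol and the matching line in the SAP, agreed before outcome data are analysed. No new data are needed, and site adjustment uses one degree of freedom.

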## Methods: patients, intervention, and outcomes

### Study design

The study is a two-center, parallel-group, randomized, superiority trial comparing osteosynthesis with non-surgical treatment following a displaced PHF in patients aged 50–65 years with a 1:1 allocation ratio.

The protocol will follow the PREPARE trial guide [18] and the SPIRIT checklist [19]. PRECIS-2 assessment indicates that the trial is pragmatic with 42 points out of 45 points (see Supplementary information, file 1) [20]. The study will be reported according to the CONSORT checklist [21]. The statistical analysis plan (Supplementary information, file 2) will follow the Guidelines for the Content of Statistical Analysis Plans in Clinical Trials [22]. All checklists are available in Supplementary information, file 3.

The trial flow and timeline for data collection are outlined in Fig. 1 and Table 1.

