#### Oxford Shoulder Score

OSS is a patient-reported shoulder-specific outcome measure to assess shoulder function. It consists of 12 questions on a 5-point Likert scale (both pain- and function-related), each offering five ordinal response options. The cumulative score ranges between 0 and 48, being 0 (worst) to 48 (best, no pain, or functional limitation). The questionnaire includes a mix of functional ability and pain-related questions. It is validated in adults with shoulder pain from a degenerative or inflammatory condition (median age 57.4 in the UK) [26], and in Denmark in patients with post-traumatic shoulder diseases, including impingement and sequelae after PHF [27]. Patients in follow-up cohorts do not need to attend the clinic in person to complete the OSS [27].

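### The primary t-test on 12-month OSS may be replaced after a normality check with no stated criterion, and the alternatives would not estimate the 9.6-point mean difference the trial is sized on

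*Protocol article*

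**What the plan says.** The Statistical analysis section of the protocol article assigns OSS at 12 months to a two-sample t-test in the intention-to-treat population. The next sentence reads "Normality assumptions will be assessed, and if violated, alternative methods such as transformation or non-parametric" and goes on to name the Mann–Whitney U test, all as options to be considered. It does not say how normality is judged, what counts as a violation, which alternative takes precedence, or what effect measure would accompany it.

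The same section plans linear mixed models in addition, with contrasts for between-group differences at given time points. It also tabulates OSS by mean, SD, median and IQR, depending on the distribution. It refers to a statistical analysis plan (Supplementary file 2), which was not available for this review.

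On the scale, the Oxford Shoulder Score section states: "The cumulative score ranges between 0 and 48". On the target, the Sample size and power considerations section states that "a relevant difference of 9.6 was assumed to represent a clinically meaningful difference". The MCID section of the Discussion adopts the same 9.6 points as the threshold for a worthwhile benefit of surgery.

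**The concern.** The trial is sized and interpreted on one quantity, a difference in mean OSS points. The primary test is not tied to that quantity. If the check is judged to fail, the primary result could be a rank-based p-value or a difference on a transformed scale. Neither says whether surgery gains 9.6 points, which the Discussion treats as the question.

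The decision would also be taken on the outcome data and by judgement. At least three primary tests are possible: the t-test, a t-test after some transformation, and Mann–Whitney U. Because the alternatives are given only as examples, others are not excluded. With a score capped at 48 and a planned SD of 12, a failed check is a realistic prospect if patients recover well. With arm means of 28 and 37.6, for example, the better arm lies 48 − 37.6 = 10.4 points below the ceiling, or 10.4/12 = 0.87 SD. A normal distribution there would put about 19% of scores above the maximum.

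**Working it through.** **Inputs from the protocol article.** Difference 9.6. SD: "The standard deviation (SD) for OSS has been reported as 12". Design: "with a power of 80% and a 5% level of significance, a sample size of 25 patients per group is required", "with a 1:1 allocation ratio". Attrition: "Assuming for a 15% potential loss to follow-up, the recruitment target is 30 patients in each group". Sidedness is not stated, and the null hypothesis is directional (surgery "is not superior to non-surgical treatment").

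**Step 1: reproduce the stated sample size.** n per group = 2(z₀.₉₇₅ + z₀.₈₀)² × SD²/Δ² = 2 × (1.960 + 0.842)² × 144/92.16 = 24.5, so 25. The t-distribution version gives 25.5. A one-sided 5% test would need only 20, so the stated 25 is a two-sided figure. Allowing for 15% loss, 25/0.85 = 29.4, so 30 per group and 60 in total. The plan's figure reproduces. Power at 25 per group is 80.7% (normal) or 79.1% (t). This calculation concerns a difference in means.

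**Step 2: how often might a normality check fail?** The article gives neither expected 12-month means nor a criterion, so both are assumptions here. The trigger was Shapiro–Wilk at 5% in either arm, with 25 per arm, rounded 0–48 scores and 10,000 simulated trials per setting. Two shapes were used: a scaled beta, and a normal with values beyond the bounds set to the bound. SD was 12 before any truncation.

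| Arm means (assumed) | Trials with at least one arm flagged |
|---|---|
| 24 and 24 | 7–21% |
| 30 and 30 | 15–53% |
| about 35 in both | 73–98% |
| about 38–40 in both | 98–100% |
| 20 vs 29.6 | 12–41% |
| 25 vs 34.6 | 36–85% |
| 28 vs 37.6 | 66–99% |
| 30 vs 39.6 | 84–100% |

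The lower figure in each range comes from the truncated normal and the higher from the beta. A normal centred at 35 before truncation gave about 60%, so a fair summary for means of about 35 or more is 60–100%. A smaller SD lowers the rate: with SD 8 and both means at 30 it was 16%.

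**Step 3: error rates in the same simulations, 25 per arm.**

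| Approach | Type I error |
|---|---|
| t-test always | 4.6–5.4% |
| Two-stage rule applied mechanically (Mann–Whitney U if flagged) | 4.8–5.8% |
| Whichever of t-test and Mann–Whitney U is significant | 5.5–7.6% |

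The two tests disagreed on significance in 1–5% of trials under the null and 3–11% under the alternative.

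**Step 4: power for the planned difference.** The t-test had 77–81% and Mann–Whitney U 76–91%. In the truncated-normal settings the cap shrinks both the SD and the realised difference (8.2–9.1 points), so these are powers for a planned 9.6 before truncation. If the data were in fact normal, Mann–Whitney U would need 25/0.955 = 26.2, so 27 per group (asymptotic relative efficiency 0.955).

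**Step 5: what each result estimates.** The t-test gives a mean difference in OSS points, directly comparable with 9.6. Mann–Whitney U concerns the chance that a patient in one arm scores higher than a patient in the other. A transformed-scale difference is in other units. Only the first answers the question on which the trial was sized.

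**The case against.** Several stronger readings are tempting, and the documents do not support them.

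- **That a switch is laid down.** It is not. The t-test is the named primary test and alternatives are only to be considered. A graphical check fits the wording as well as a formal test.
- **That the switch will almost always happen.** This needs 12-month means near the ceiling, which the article does not give. Across the assumed settings the rate ran from about 7% to 100%. The beta model with a large SD and a high mean also piles scores at 48, a shape the article does not establish.
- **That the mean difference is lost.** The mixed-model contrasts and tabulated means keep it available. It would lose its standing as the primary inference. The mixed model is described as additional and partly exploratory, and the tabulation may itself depend on the distribution.
- **That type I error is inflated or power lost by the rule itself.** Neither is shown. The 5.5–7.6% arises only if the test is chosen by its result, which the article does not license but does not prevent.

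The article also provides for analysis on anonymised data, supervision by a biostatistician, and abstracts written before the arms are revealed. These limit choices that favour a particular arm. They do not prevent choice by significance, because p-values are visible without knowing which arm is which.

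The strongest objection is that the analysis plan may define the check and the fallback. If so, the element of discretion goes. The article would still make the primary test, and with it the quantity estimated, depend on the outcome data. That is a rule stated in the article rather than a detail left out of it.

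**Conclusion.** The point holds in a limited form. The article lets the primary test change on an undefined look at the outcome data, and the named alternatives do not estimate the 9.6-point mean difference that justifies the sample size and sets the clinical threshold. The harm is an unfixed target of inference and room for choice. A mechanical rule would not materially affect error rates. Discretionary choice between the two tests could raise type I error to about 5.5–7.6%.

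The switch also buys little protection, since the t-test performs adequately on bounded, skewed scores at 25 per arm. All simulated figures rest on assumed arm means, two assumed score shapes and an assumed Shapiro–Wilk trigger. The mismatch between the rank or transformed result and the 9.6 points does not depend on those assumptions.

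**What to change.** Delete the normality-triggered switch from the Statistical analysis section. State that the primary analysis is the between-group difference in mean 12-month OSS, in points with a 95% CI, by Welch t-test or an equivalent mean-based method, whatever the distribution. Keep Mann–Whitney U, or a bootstrap CI for the mean difference, as a named sensitivity analysis. Align the analysis plan if it repeats the conditional wording, and make the change before any comparative outcome data are seen.

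The cost is one sentence. The sample size stays at 25 evaluable and 30 recruited per group. The small downside is that, if scores are strongly skewed, the rank test's possibly higher power (up to 91% against about 81% in the most skewed setting simulated) is not used for the primary test.
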